## Abstract

**Background:**

Individuals transitioning from homelessness to housing face challenges to reducing alcohol, drug and HIV risk behaviors. To aid in this transition, this study developed and will test a computer-assisted intervention that delivers personalized social network feedback by an intervention facilitator trained in motivational interviewing (MI). The intervention goal is to enhance motivation to reduce high risk alcohol and other drug (AOD) use and reduce HIV risk behaviors.

**Methods/design:**

In this Stage 1b pilot trial, 60 individuals that are transitioning from homelessness to housing will be randomly assigned to the intervention or control condition. The intervention condition consists of four biweekly social network sessions conducted using MI. AOD use and HIV risk behaviors will be monitored prior to and immediately following the intervention and compared to control participants’ behaviors to explore whether the intervention was associated with any systematic changes in AOD use or HIV risk behaviors.

**Discussion:**

Social network health interventions are an innovative approach for reducing future AOD use and HIV risk problems, but little is known about their feasibility, acceptability, and efficacy. The current study develops and pilot-tests a computer-assisted intervention that incorporates social network visualizations and MI techniques to reduce high risk AOD use and HIV behaviors among the formerly homeless.

**ClinicalTrials.gov Identifier:**

NCT02140359.

## Background

Homeless individuals have significantly higher rates of morbidity and mortality as compared to those living in stable housing [1–4]. Among the most pressing health issues facing homeless individuals are the interrelated problems of alcohol and other drug (AOD) use and HIV risk. An estimated 30–50 % of homeless individuals are AOD dependent [5, 6]. AOD use is both a leading cause of homelessness [5] and is exacerbated by the stress of life on the street and exposure to high rates of AOD use among other homeless people [6–8]. Exposure to HIV is a significant health threat for homeless individuals, with rates of HIV infection being three to nine times greater among homeless persons than those with stable housing [4, 9, 10]. The greater vulnerability to HIV among homeless individuals is due, in part, to AOD use increasing their likelihood of engaging in risky sexual behaviors such as having unprotected sex and trading sex.

Given the association between homelessness and poorer health, the provision of stable housing is often seen as an important health intervention [11]. There are two main approaches to housing provision to homeless individuals: programs that make housing contingent on AOD abstinence and treatment participation (i.e., “treatment first” (TF) approaches [12–14]) and programs that provide housing without the abstinence requirement, known as Housing First (HF) approaches [15–17]. Studies have demonstrated that HF residents have similar [18] or improved [17, 19] AOD outcomes after 1–2 years compared to TF residents. Further, HF participants have a 53 % reduction in health service expenses compared to those on waiting lists [20]. Due to these encouraging findings, HF programs have flourished over the past two decades, there are now 100s of HF programs located across the United States [15, 17, 21, 22], and HF programs are now being developed and tested outside of the United States [23].

Although there is promise that HF programs can successfully provide housing without requiring AOD use abstinence, there are still concerns that HF programs are not necessarily a panacea to homelessness [15] and that these programs may be more helpful for those with less severe AOD use [12]. One concern raised is that individuals attempting to abstain from AOD use are inadvertently exposed to high-risk behavior because of the policy of not requiring abstinence in the environment in which the resident is living [15]. This may be particularly challenging in project-based HF models where individuals reside nearby others engaging in high risk behaviors. In these programs, HF residents may require support to face the challenge of entering a new social environment that includes a mixture of AOD users and non-users.

### Social networks and health interventions

A social network based intervention [24] may be a promising approach to enhance the positive behavioral outcomes associated with these programs. Social networks are naturally occurring groups of people which can be characterized in terms of their composition (defined as the quantity and type of individuals in a network) and social network structure (defined as the connections among network members) [25]. Social networks have the potential to influence health behaviors and outcomes through social comparison, social sanctions and rewards, information transmission, support and resources, stress reduction, and socialization [24–29]. A large and growing body of research demonstrates both the positive and negative influences of social network on the lives of homeless individuals [30–32], including their health and health-related behaviors [7, 9, 33, 34]. For example, social networks are an important source of social support and thus may influence (positively or negatively) AOD use, HIV risk behavior, AOD treatment program participation, and successful transition out of homelessness [6–8, 17, 33–39]. The social networks of homeless individuals tend to be compositionally diverse, often including non-homeless individuals who influence AOD behavior [7, 40–43] and a mixture of risky and non-risky influences and sources of potential social support [7, 44]. These networks tend to be structurally diverse as well [44, 45], with a range of interconnections among high-risk and/or supportive network contacts [46].

Given these findings, targeting the social networks of HF residents may be a promising approach to support the transition from homelessness and reduce AOD- and HIV-related risk behaviors. Social network based interventions have shown promise in changing health behaviors [24]. For example, studies have successfully changed substance use behavior of adolescents through use of social network analysis to identify highly central peers to lead the interventions [47, 48]. Other experimental studies that have manipulated social network exposures have produced evidence of changes in behavior related to seeking health information through peer influence [49]. However, there are limitations to incorporating existing social network intervention approaches into HF programs. Most existing network-based AOD interventions primarily target the composition of networks. For example, many are based on abstinence and/or focus on developing new social networks with other abstaining network contacts [50–56]. These interventions are only applicable to those who are already abstaining from AOD use. Few social network based interventions target changes to network structure [57]. Those that account for network structure are primarily educational interventions that use social network analysis to track the impact of the intervention throughout the network [24]. In this approach, key individuals in the group are selected to receive an intervention because of their central network position and greater likelihood of spreading the intervention to their peers. This approach would not address the diversity of network contacts for homeless people or the shifts in network composition and structure they are likely to experience as they transition into HF programs. New HF residents are likely to face a reduction in their contact with homeless peers, increased contact with persons who reside close to them, and possibly reconnect with network members from their past.

### Personal network visualizations

This study involves designing a personalized social network intervention that targets behavioral change through personal network visualization presentations by a facilitator trained in motivational interviewing (MI) [45]. We hypothesize that a social network-based intervention that focuses on HF residents’ *personal networks* could assist individuals in making positive compositional changes (i.e., adding and/or removing types of network members) and structural changes (i.e., strengthening, weakening, adding connections among network members) to their networks that are associated with reduced AOD use and HIV sexual risk behaviors. Providing feedback on personal network composition and structure may be useful for individuals transitioning to supportive housing. As they begin to make a major shift in their physical surroundings, they can better understand their current social environment (who they are currently connected to, what types of behaviors they engage in, how these people are connected to each other) to help guide their interactions with these people in the future. To date, we are unaware of any social network interventions that target the diversity of social contacts and social structure experienced by people as they transition from homelessness.

Personal network interviews can be enhanced with visualizations of the networks to trigger additional discussion about the network dynamics of a respondent [45, 58–60]. Personal network visualizations allow for display of both compositional and structural features of the network. For example, interview participants can see who within their networks is engaging in risky behavior, providing them with support, and how these different types of individuals are connected to each other. These visualizations are easy to understand and have been used with homeless participants with less than high school education [41, 45]. Although it is often assumed that the presentation of network visualizations can lead to behavior change [24], to our knowledge these types of visualizations have not been incorporated into AOD use and HIV risk reduction interventions. Network visualizations are not new to health-related interventions. Visualization tools have been used by social workers to provide feedback to families about health and social support [61, 62]. However, these techniques only provide information about network composition and do not incorporate structure. Network visualizations that incorporate structure have been used in a study of an educational intervention that promoted interactions among adolescents [63]. This study found that presentation of network visualizations prompted students to become more strategic about how they formed connections to other students to improve their learning performance. We hypothesize that HF residents could be impacted in a similar way.

### Computer assisted motivational interviewing

Presenting visual personalized social network feedback to participants using MI may be an ideal approach to help participants explore changes to their social network and risk behaviors. MI is an evidence-based intervention style [64] that has been used to reduce AOD abuse and HIV risk behavior [57]. More specifically, MI is a client-centered, directive therapeutic approach to enhance readiness for change by helping individuals explore and resolve ambivalence [65]. Adapted from self-perception theory that posits that people become more committed to a position that they hear themselves state [66], MI seeks to elicit “change talk”—individual expressions of desire, ability, reasons, and need for change. MI facilitators are instructed to respond using “reflective listening”, which is to offer periodic summaries of an individual’s self-motivational statements [67]. As a result, individuals hear themselves explain their own motivations for change, and also hear them reflected back again by a MI facilitator thereby increasing desire and commitment to changing a behavior. Recently, one existing MI intervention has been enhanced with a social network component [57]. However, currently, there are no MI interventions to our knowledge that take into account both compositional and structural characteristics of social networks with visualizations and none that target HF residents.

Developing a computer-assisted tool for delivering a social network intervention may provide a cost-effective way of disseminating it. Computer-assisted intervention delivery tools offer low cost options for adoption in community settings and improve fidelity to intervention delivery procedures [68] using a variety of computer sources such as laptops and tablets. Use of a tool to collect and present personal network information can also allow individuals to visualize how their personal networks change over time, which may provide tangible evidence that the steps they are taking to make changes are having an effect, reinforcing the intervention’s benefits.

### Study design, aims and hypotheses

This study was designed to explore whether employing a MI approach to present personal network information electronically would help HF residents transition away from high-risk social networks and toward low-risk, supportive social networks and result in less risky AOD use and sexual behaviors. Consistent with the stage model approach to behavioral therapy intervention development [69], the study consists of two phases, a development phase (i.e., Stage 1a) and a pilot test phase (i.e., Stage 1b). The Stage 1a development work has been completed and consisted of developing and iteratively testing the intervention to assess usability, feasibility and acceptability among residential support services staff and HF residents. Data analysis of qualitative data generated during Stage 1a is ongoing and will be reported elsewhere. This paper describes the design of the Stage 1b pilot test of the intervention.

The aim of the pilot study is to generate preliminary evidence about the effectiveness of the intervention on reducing AOD use and HIV risk behaviors. To meet this aim, 60 residents with past year harmful AOD use will be randomly assigned to receive the intervention or usual care. The justification of a sample size of 30 per study condition is based on published guidelines for conducting Stage 1b clinical trials which are considered pilot studies, developmental in scope, and exploratory in nature [69]. We will analyze baseline (i.e., pre-intervention) and follow-up (i.e., post-intervention, approximately 90 days from baseline) data to determine the feasibility, acceptability and promise of the intervention for a subsequent Stage 2 efficacy trial [69].

We will explore the following hypotheses: intervention participants, compared to control participants, will show: (a) increased AOD use and safe sex-related self-efficacy (b) increased readiness to change AOD use and high-risk sexual behavior, (c) social networks with fewer and less central high-risk members at the follow-up assessment and (d) significant reductions in AOD use and fewer HIV sexual risk behaviors between the baseline and follow-up period compared to control participants. We examine self-efficacy and readiness to change as those appear to be the psychological constructs that MI is designed to address. We hypothesize that the motivational social network intervention will increase self-efficacy and readiness to reduce AOD use and HIV risk behaviors. We will also explore whether the proximal outcomes (i.e., greater efficacy, greater readiness to change, and reductions in the riskiness of networks) appear to mediate the relationship between the intervention and the distal outcomes (i.e., changes in high-risk behavior). At the end of this study, we will have an electronic tool for delivering a motivational network intervention (MNI), a well-described set of procedures for conducting the MNI intervention, and preliminary data for a possible future efficacy trial.

## Methods

### Setting

The study is being conducted in collaboration with Skid Row Housing Trust (SRHT) and Single Room Occupancy Housing Corporation (SRO Housing), two of the largest HF providers in Los Angeles County. Both organizations combine the HF framework for providing rapid housing with minimal preconditions with permanent supportive housing (PSH) to many of its residents [70]. PSH is long-term community-based housing linked with voluntary supportive services for individuals with disabilities who have experienced homelessness. SRHT and SRO Housing manage properties in the Skid Row area of downtown Los Angeles, which has the largest concentrations of homeless adults in Los Angeles County.

### Participants, eligibility and recruitment

Participants will include recently housed residents aged 18 or older who are (1) able to speak and understand English, (2) are not cognitively impaired (based on administration of the Short Blessed Scale Exam during screening for eligibility [71]), and (3) screen positive for past-year harmful AOD use (either drugs or alcohol) using the Alcohol Use Disorders Identification Test (AUDIT-C) (a score >4 for men and >3 for women) [72] and the Drug Abuse Screen Test (DAST) (a score >2) [73–75]. Recruitment, screening for eligibility, and assessment procedures are depicted in Fig. 1.

**Fig. 1 Fig1:**
[figure not shown]
Study design and procedures

Leasing staff will be instructed to introduce the study to all housing applicants that have recently received assignment to a housing unit. Those who express interest in being contacted for the study will be given a consent-to-be-contacted form to complete. Leasing office staff will share the completed consent-to-be-contacted form with the research team. Next, the research team will attempt to contact the potential participant by phone to complete a study screener. If a resident is interested in the study but does not have access to their own phone, the leasing staff will provide access to a phone. If the resident does not contact research staff by phone at leasing and does not provide a working phone number on the consent-to-be-contacted form, a member of the research team will attempt to locate the resident at their residence and provide access to a phone to complete the study screener. Once an interested resident is connected by phone for screening, the research team will describe the study, obtain consent to conduct the screener, and conduct the screener interview to determine eligibility. Next, eligible participants will be asked to schedule an in-person study consent and baseline assessment. Participants will also be contacted for a follow-up assessment 3 months after baseline. Residents will be provided with study appointment cards to assist them in recalling their appointments. Participants will be paid $30 for the baseline (i.e., pre-intervention) assessment and $40 for the follow-up (i.e., post-intervention, approximately 90 days after baseline) assessment.

### Randomization

After participants complete the baseline assessment, they will be assigned to one of two experimental conditions (i.e., intervention or control). We aim to randomly assign 60 participants using a stratified permuted block randomization strategy. Given the relatively small sample size, the randomization might produce an unbalanced assignment with respect to gender. For this reason the randomization will be stratified. About 26 % of SRHT clients are women and stratifying on this characteristic will ensure an approximately equal number of women assigned to both conditions. If the intervention and control groups turn out to be unbalanced with respect to other characteristics, we will use covariate adjustment at the analysis phase. Next, participants assigned to the intervention arm will be contacted by project staff by phone to schedule the four MNI sessions, one every 2 weeks. If the participant is difficult to reach by phone, a project staff member will attempt to contact the participant by visiting their residence to schedule their first session. Participants will be provided with appointment cards as reminders. Participants will be given a $5 food gift card for each intervention session they attend.

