### Analyses

Given the planned sample size (i.e., n = 60), sophisticated modeling and adjustments for non-response might not be possible, and the bulk of the analyses will be primarily descriptive. We will estimate the outcomes’ variability in this population and more generally assess the hypothesized trends to determine the intervention promise and identify potential mediators for future studies. Analyses will use the standard intent-to-treat (ITT) approach to examine the effect of offering the MNI intervention to eligible and consented participants. We will attempt to follow up with all participants, regardless of their MNI participation. Our ITT approach will analyze participants as belonging to the group they were randomized to, regardless of their compliance, because excluding those who do not complete the MNI would bias results in favor of MNI, increasing type I errors [109].

We will be able to obtain intervention effect estimates on both the proximal (i.e., efficacy and readiness to change AOD, safe-sex behavior, and networks) and distal outcomes (i.e., AOD use and HIV risk behavior) using a difference in differences (DID) approach [110]. The DID approach is well-suited to the data generated by the adopted study design: for every subject we will have a pre- and post-intervention observation and a randomized group indicator (intervention or control). We will implement the DID approach by fitting a mixed-effects model in which participants are treated as random effects while time, the intervention group indicator, and their interaction are treated as fixed effects. This modeling approach accounts properly for the two repeated measures’ correlation on each participant and tends to produce efficient intervention effect estimates [111]. The intervention effect estimate is given by the coefficient of the interaction between the time and intervention indicators.

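### Gender is the stratification factor but is not in the stated mixed model; if men and women change differently over follow-up, the standard error is modestly too large

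*Protocol article*

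**What the plan says.** **Protocol article, Randomization.** The design is fixed: "We aim to randomly assign 60 participants using a stratified permuted block randomization strategy". The reason is that, with a small sample, "the randomization might produce an unbalanced assignment with respect to gender", and the section concludes: "For this reason the randomization will be stratified". The section expects the following: "About 26 % of SRHT clients are women and stratifying on this characteristic will ensure an approximately equal number of women assigned to both conditions". Gender is the only stratification factor named. The section then provides that if the arms turn out "unbalanced with respect to other characteristics, we will use covariate adjustment at the analysis phase".

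**Protocol article, Analyses.** The effect is estimated by difference in differences from a mixed model in which "participants are treated as random effects while time, the intervention group indicator, and their interaction are treated as fixed effects". The time-by-group coefficient is the effect estimate. Gender is not among the listed terms.

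**Protocol article, Baseline measures.** Gender is collected with the other demographics, for description, for comparing the arms and possibly for exploring moderators.

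**The concern.** When allocation is forced to balance on a factor, that factor's contribution to the arm difference is removed by design. A model without the factor still counts its variation as residual noise, so the reported standard error can exceed the real variability of the estimate. The usual remedy is to carry the stratification factor into the model.

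Here the listed fixed effects leave gender out. The adjustment rule does not bring it back, because it concerns other characteristics and applies only after an imbalance is seen. At stake is precision: intervals somewhat wider than they need be, in a pilot meant to estimate outcome variability and judge the promise of the intervention for a later efficacy trial.

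**Working it through.** The article gives no power calculation or standard error, so there is no figure of its own to reproduce.

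**Inputs from the article**
- 60 participants, 30 per arm; one baseline and one follow-up value each.
- About 26% women among clients of one of the two housing providers. If this carries over to the trial (assumption; the other provider's share is not given), 0.26 × 60 = 15.6 women, or 7.8 per arm.

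**Assumed inputs**
- *d*, the difference between men and women in mean change, in units of the within-gender SD of change.
- For the simulation: 16 women split 8/8, outcome SD 1 and within-person correlation 0.5. The SD of change is then √(2 × (1 − 0.5)) = 1, so *d* is also in outcome SDs.

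**Step 1: what the coefficient estimates.** With complete pairs, the time-by-group coefficient is the arm difference in mean within-person change. A gender difference that is the same at both visits drops out of each person's change. Refitting the stated mixed model to two simulated data sets confirmed this:
- Gender level effect of 1.5 SD: standard error 0.2307 without gender, and 0.2307 with a gender main effect.
- Gender difference in change of 1.0 SD: 0.2710 without gender, 0.2710 with a main effect, and 0.2414 with gender-by-time added.

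The point estimate was the same in all three fits of each data set.

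**Step 2: size when change differs by gender.** With gender balanced between arms, the true SD of the estimate is σ√(2/30), which is 0.2582 for σ = 1. The model without gender sees a variance of change of σ²(1 + p(1 − p)d²), where p(1 − p) = 0.26 × 0.74 = 0.1924. Hence:

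overstatement of SE = √(1 + 0.1924 d²) = 1/√(1 − R²), where R² is the share of the variance in change explained by gender.

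- R² = 2%: 1/√0.98 = 1.010, which needs d = √(0.0204/0.1924) = 0.33.
- R² = 10%: 1/√0.90 = 1.054, which needs d = √(0.1111/0.1924) = 0.76.

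**Step 3: simulation.** There were 20,000 trials per row, analysed on change scores. Type I error is at a nominal two-sided 0.05, and power is at an assumed effect of 0.75 SD. *With* and *without* refer to the gender-by-time term.

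| d | SE ratio, formula | SE ratio, simulated | Type I without / with | Power without / with |
|---|---|---|---|---|
| 0.25 | 1.006 | 0.2585/0.2561 = 1.009 | 0.047 / 0.049 | 0.81 / 0.81 |
| 0.5 | 1.024 | 0.2637/0.2601 = 1.014 | 0.046 / 0.051 | 0.80 / 0.81 |
| 1.0 | 1.092 | 0.2820/0.2582 = 1.092 | 0.030 / 0.050 | 0.76 / 0.81 |
| 1.5 | 1.197 | 0.3101/0.2575 = 1.204 | 0.019 / 0.047 | 0.68 / 0.81 |

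With a level effect of 1.5 SD and no difference in change, the mean standard error was 0.257 with or without the term, and type I error was 0.048 in both.

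**Step 4: cost of the term.** On change scores, residual degrees of freedom go from 60 − 2 = 58 to 60 − 3 = 57. If gender explains nothing in the sample, the standard error rises by at most about √(58/57) = 1.009. With no gender effect at all, the simulated mean standard error was 0.2568 either way.

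These figures are for continuous outcomes with complete pairs. They do not carry over directly to binary outcomes.

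**The case against.** The strongest reply is that this is a condensed article, that covariate lists normally sit in an analysis plan, and that naming the core terms does not rule out others. Part of that stands: a fuller plan could add gender. But the article is not silent. It lists the fixed effects and states an adjustment rule, and neither includes the factor it randomizes by.

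Four stronger readings are tempting, and the documents do not support them:
- *The standard error is too large whenever gender predicts the outcome.* It is not. The estimate compares within-person change, so a level difference cancels with complete pairs. With missing follow-up the cancellation is only approximate. Nothing in the article says that men and women change differently.
- *The results would be biased or too often positive.* They would not. The omission does not bias the estimate, and type I error moves below 0.05, not above it.
- *Gender is ignored throughout.* Baseline measures lists it for arm comparison and possible moderator analysis. What is missing is gender in the main model.
- *The article treats gender as prognostic.* Its stated aim is only that "stratifying on this characteristic will ensure an approximately equal number of women assigned to both conditions".

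It is also fair that the analyses are described as mainly descriptive, that no stated decision turns on a few per cent of interval width, and that extra terms can be unstable for sparse binary outcomes with so few women. These points lower the importance of the finding and shape the remedy. They do not remove the mismatch.

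**Conclusion.** The point holds, and it is minor. Randomization is stratified by gender, while the analysis as written has only "time, the intervention group indicator, and their interaction are treated as fixed effects". If gender is related to change, the standard error is too large by about 1% to 5% for R² of 2% to 10%, which corresponds to a gender difference in change of about 0.33 to 0.76 SD. It reaches about 9% only at a difference of 1.0 SD. If gender is unrelated to change, nothing is lost by the omission and essentially nothing is gained by the term. The size rests on three assumptions: the gender difference in change, the 26% share of women carrying over to the trial sample, and complete pairs.

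**What to change.** In Analyses, state that the mixed model for each outcome will contain fixed effects for gender and gender-by-time beside time, group and time-by-group, whether or not an imbalance is observed. A gender main effect alone is not enough, because it leaves the time-by-group estimate and its standard error unchanged. Add a simplification rule set in advance: where a binary outcome is too sparse for a stable fit with about 8 women per arm, the gender terms are reduced or dropped, and this is reported.

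The difference-in-differences approach stays as it is, and gender is already collected. The cost is a sentence or two and about one degree of freedom on the effect estimate (58 to 57 with complete pairs).

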### Baseline measures

We will assess baseline *demographic characteristics* (i.e., age, gender, race/ethnicity, education, number of children, marital status, income) and history with homelessness to describe the study population, explore whether there are any differences between the participants assigned to the different study conditions, and potentially explore as potential intervention effect moderators.

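### Covariate adjustment is triggered by observed imbalance, and baseline covariates entered as main effects would leave the planned time-by-group estimate unchanged (linear model, complete pairs)

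*Protocol article*

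**What the plan says.** The Randomization section stratifies on gender only, on the ground that "stratifying on this characteristic will ensure an approximately equal number of women assigned to both conditions". For everything else it gives a conditional rule: if the arms "turn out to be unbalanced with respect to other characteristics, we will use covariate adjustment at the analysis phase". It names no covariates, no criterion for imbalance and no form of adjustment.

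The Baseline measures section lists seven demographic items (gender among them) plus homelessness history. One stated use of them is to "explore whether there are any differences between the participants assigned to the different study conditions".

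The Analyses section describes a difference-in-differences analysis by mixed model, in which "participants are treated as random effects while time, the intervention group indicator, and their interaction are treated as fixed effects". It then says: "The intervention effect estimate is given by the coefficient of the interaction between the time and intervention indicators". It takes it that "for every subject we will have a pre- and post-intervention observation and a randomized group indicator", but also warns that "sophisticated modeling and adjustments for non-response might not be possible".

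**The concern.** There are two separate difficulties.

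- **The trigger.** Whether to adjust, and for what, is decided after the arms have been compared. A covariate matters when it predicts the outcome (here, change in the outcome), whether or not its arm difference looks large. With no covariates and no threshold fixed, the final model stays open for self-efficacy, readiness, network, substance-use and sexual-risk outcomes alike.
- **The form.** The usual way to adjust is to add the baseline characteristic as a main effect. In the model the article fixes, that term has nothing to act on in the effect estimate.

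The article uses these estimates to judge promise for a Stage 2 trial. A result labelled as adjusted that equals the unadjusted one would give reassurance it has not earned.

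**Working it through.** **Inputs from the article.** 30 participants per arm, one pre and one post observation, random participant effect, fixed time, group and time-by-group. It gives no effect size, SD, dropout rate or covariate slope, so there is no figure of its own to reproduce. The covariate imbalance, slopes and dropout rates below are assumptions.

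**Step 1: algebra.** Write the linear model with a baseline covariate x as a main effect:

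Y(i,t) = b0 + b1·t + b2·G + b3·t·G + c·x(i) + u(i) + e(i,t)

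The change for participant i is D(i) = b1 + b3·G + e(i,1) − e(i,0). Both c·x(i) and u(i) cancel. With complete pairs, the estimate of b3 is mean D in the intervention arm minus mean D in the control arm, with or without x.

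If x also predicts change with slope d, D(i) gains the term d·x(i). Given an arm difference m in the mean of x, the estimate is then centred on b3 + d·m. The main effect leaves d·m in place; a covariate-by-time term removes it.

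| Slope d | m = 0.25 SD | m = 0.5 SD |
|---|---|---|
| 0 | 0 | 0 |
| 0.25 | 0.06 | 0.125 |
| 0.5 | 0.125 | 0.25 |

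**Step 2: simulation, complete pairs.** 150 data sets per row, true effect -0.40, assumed mean imbalance 0.5 SD. The simulated outcome has a within-arm SD near 1.

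| Slope on change | Unadjusted | Main effect added | Covariate-by-time added | Mean SE, unadjusted |
|---|---|---|---|---|
| 0 | -0.387 | -0.387 | -0.385 | 0.256 |
| 0.5 | -0.114 | -0.114 | -0.385 | 0.286 |

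Over the 300 data sets the main effect changed the estimate by at most 2.6e-15 and its SE by at most 0.005. In the second row the shift is 0.387 − 0.114 = 0.273. Divided by 0.5 this gives a realised average imbalance of about 0.55, which is why the shift is slightly more than the 0.25 in the table above.

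**Step 3: missing follow-up, slope 0.5.** Missingness was made to depend on the covariate.

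| Assumed missing | Unadjusted | Main effect | Covariate-by-time |
|---|---|---|---|
| 10% | -0.119 | -0.119 | -0.390 |
| 20% | -0.119 | -0.118 | -0.387 |
| 30% | -0.136 | -0.129 | -0.393 |

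Across both slopes, the main effect now moves single estimates by 0.02 to 0.06 on average (largest 0.20). The mean hardly moves, and the distortion remains.

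**Step 4: other links.** In a marginal logistic model the interaction moved from a mean of -0.505 to -0.569 when the main effect was added. The covariate had no effect on change in that simulation, so the movement reflects the logit scale and not a correction. In a log-linear count model the interaction did not move.

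**Step 5: how often the trigger would fire by chance.** Treat the eight listed characteristics as independent.

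- At least one with p < 0.05: 1 − 0.95^8 = 0.34.
- One standardized difference above 0.25: the SE is √(2/30) = 0.258, so 0.25/0.258 = 0.97, two-sided probability 0.333. At least one of eight: 1 − 0.667^8 = 0.96.
- Without gender, which is stratified: 1 − 0.95^7 = 0.30 and 1 − 0.667^7 = 0.94.

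Whether adjustment happens therefore depends largely on a threshold the article does not state.

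**The case against.** The strongest reply is that the article never says covariates would enter as main effects. A covariate-by-time term is also covariate adjustment, and a condensed article may leave the form to a fuller plan. This stands. A reader might infer that the safeguard cannot work, or that adjusted and unadjusted results will always be identical; the documents do not support either. The identity needs a main effect, a linear model and complete pairs. The article itself expects some non-response, and sexual-risk outcomes such as concurrent partnerships may be binary.

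Other points also stand:

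- Difference-in-differences already removes a baseline difference in outcome level that stays constant. Only a covariate that predicts change is at issue.
- Under randomization the unadjusted contrast is unbiased on average. What is shown is error given the imbalance that occurred.
- A 0.5 SD gap is about 1.94 SEs (0.5/0.258), roughly a 5% event for any one covariate. The shift of 0.273 is smaller than one SE of the estimate (0.286).
- A reader might take the article to call imbalance likely. It says only that it might arise, with respect to gender, and it deals with that by stratifying.

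The trigger is not answered by any of this. The article was not silent on it: it committed to a data-dependent rule, and a later plan that fixed covariates in advance would depart from that wording.

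**Conclusion.** The point about the trigger holds as written: covariates are to be chosen on observed imbalance, with neither the candidates nor a criterion fixed. The point about form holds conditionally. If the covariate is a main effect in the stated linear model with complete pairs, the effect estimate cannot change, and chance imbalance on a characteristic that predicts change goes uncorrected. With 10% to 30% missing follow-up the estimate can move slightly, but in the linear simulations the distortion was not removed.

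The size is the product of imbalance and slope, both assumed: zero if the covariate does not predict change, and about 0.06 to 0.25 over the range shown. The weight is limited, because this is an exploratory and mainly descriptive pilot with no confirmatory test at stake. The change is still worth making, since it replaces a stated rule with a better one at little cost.

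**What to change.** Delete the imbalance trigger. Before any outcome data are seen by arm, name a short set chosen for prognosis, to be used whatever the baseline table shows and for all outcomes. Gender (the stratification factor) and housing provider (the two organizations in the Setting section) are examples. Then state one of two forms:

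- **Keep the planned mixed model** and add each covariate together with its interaction with time.
- **Use a follow-up model** adjusted for the outcome's own baseline value plus these covariates. This also requires rewording the definition of the effect in the Analyses section.

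Do not enter the baseline outcome as a covariate-by-time term in the mixed model, where it is already a response.

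The cost is about two sentences and a few degrees of freedom. With complete pairs, the change comparison has 60 − 2 = 58; two binary covariates interacted with time leave 56. The follow-up model with the baseline outcome leaves 55. Adjusting for a covariate that turns out not to predict change adds a little noise: in the simulation, single estimates moved by 0.058 on average and the mean stayed put (-0.387 and -0.385).
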